### Usual Medical Care Group

Participants will take part in a pragmatic 12-week medical intervention led by a family physician, consisting of up to 3 consultations during this period. The initial in-person meeting at the medical clinic will involve a comprehensive evaluation by the family physician, which may include diagnostic clinical tests, laboratory tests, and medical imaging if necessary. Based on this assessment, the family physician and participant will collaboratively determine the most appropriate management approach. Interventions may range from reassurance and patient education on pain management strategies to pharmacological treatments and corticosteroid injections. If needed, the family physician may refer participants to a physiotherapist, medical specialist, or other health care providers (eg, psychologists, occupational therapists, kinesiologists, acupuncturists, or chiropractors). However, these referrals will not be managed by the research team, and the associated costs will be the participant's responsibility.

During the 2 potential follow-up meetings, the participant’s condition will be reassessed, and the intervention will be adjusted accordingly. While these meetings are preferably conducted in person, they may also be held by phone or via telehealth, depending on the participant’s preference. If a participant becomes symptom-free before completing the 3 sessions, or if the participant and family physician decide that no further sessions are required, treatment will be discontinued, and appropriate advice and recommendations will be provided. However, they will have the option to resume the intervention within the 12-week period if needed. Given the pragmatic nature of the intervention, its structure remains flexible, allowing for adaptation based on the participant’s goals and preferences and clinical presentation. Following each session, the family physician will complete a brief REDCap questionnaire documenting the management approach used (eg, education, medication, and injection), any imaging or laboratory tests ordered, any referrals made, and the follow-up plan.

### Training of Treatment Providers

Given the pragmatic nature of the interventions in the usual medical care and usual rehabilitation care groups, the physiotherapists and family physicians in these groups will not receive specific training related to the intervention. However, they will attend a 60-minute meeting outlining the study objectives and relevant procedures (eg, maximum number of consultations, the brief questionnaire to be completed in REDCap, and the expectation that they provide care according to their usual practices).

Physiotherapists delivering the educational intervention were selected based on their expertise in a clinic specializing in educational approaches for MSKDs. They will participate in a 2-hour in-person training session led by 3 members of the research team. This training will emphasize the educational components to be delivered and the importance of establishing a strong therapeutic alliance with participants. The study’s educational website will also be presented and explained during this session. To ensure consistency, follow-up meetings will be held twice a year to discuss strategies for maintaining standardization and to address any challenges that arise.

It should be noted that physiotherapists and family physicians providing usual medical care and usual rehabilitation care will not have access to the educational website, nor will it be presented to them.

### Primary and Secondary Outcome Measures

#### Overview

The study outcomes will be assessed online using web-based patient-reported outcome measures on REDCap [42]. Patient-reported outcome measures integrated within REDCap are designed to prevent incomplete submissions, ensuring that all questionnaires are fully completed. The primary outcome will be functional limitations at 24 weeks, as measured with the Pain Interference subscale of the BPI-SF. Secondary outcomes include pain severity as measured with Pain Severity subscale of the BPI-SF, health-related quality of life (HRQoL) as measured with the EQ-5D-5L, pain-related fear as measured with Tampa Scale for Kinesiophobia (TSK), pain catastrophizing as measured with Pain Catastrophizing Scale (PCS), pain self-efficacy as measured with Pain Self-Efficacy Questionnaire (PSEQ), symptoms related to central sensitization using the Central Sensitization Inventory (CSI), risk of long-term disability and poor recovery as measured with the short version of the OREBRO musculoskeletal pain questionnaire (ÖMPQ-sf), and anxiety and depressive symptoms as measured with Hospital Anxiety and Depression Scale (HADS). Furthermore, region-specific symptoms and functional limitations will be assessed at all time points using the modified ODI for participants with low back pain, the NDI for those with neck pain, the QuickDASH for participants with rotator cuff–related shoulder pain, and the KOS-ADLS for those with anterior knee pain. Finally, participants’ satisfaction with the treatment will be assessed at the end of the intervention period (week 6 for the stepped care group, and week 12 for the “unresolved” participants in the stepped care, usual rehabilitation, and usual medical care groups). Validated French or English versions of all questionnaires are available. The psychometric properties of all patient-reported outcome measures have been established in populations with MSKDs [66-70]. Given the number of patient-reported outcome measures assessed at baseline, their completion will be divided into 2 sequences. The first sequence (BPI-SF, EQ-5D-5L, TSK, PCS, PSEQ, and region-specific patient-reported outcome measure) will be completed before the in-person meeting, while the second sequence (CSI-9, ÖMPQ-sf, and HADS) will be completed during the in-person meeting. Although most outcomes will be assessed at all measurement time points, some secondary outcomes will only be reassessed at 12 or 24 weeks to minimize the burden on participants. Figure 2 provides an overview of when the patient-reported outcome measures will be assessed at the different measurement time points.

#### Primary Outcome: Functional limitations

The BPI-SF is an 11-item questionnaire comprising two subscales: the 4-item Pain Severity subscale and the 7-item Pain Interference subscale. It has been shown to be valid, reliable, and responsive for MSKDs [71-74]. The Pain Interference subscale, measured at the 24-week follow-up, will be the primary outcome measure, assessing the extent to which pain disrupts daily functioning [73,74]. Its minimally clinically important difference ranges from 1.3 to 2.0 out of 10 points [58].

#### Secondary Outcomes: Generic Patient–Reported Outcome Measures

Secondary outcomes comprised pain severity, HRQoL, pain-related fear, pain catastrophizing, pain self-efficacy, symptoms related to central sensitization, risk of long-term disability, and anxiety and depressive symptoms. Pain severity: The Pain Severity subscale of the BPI-SF consists of 4 items that assess pain intensity [75]. HRQoL: The EQ-5D-5L is a 5-item generic HRQoL questionnaire evaluating five dimensions: mobility, self-care, usual activities, pain and discomfort, and anxiety and depression. These dimensions define 55=3125 possible health states, which can be converted into a Canadian weighted index score [76]. The weighted index scores at each time point will be used to calculate the quality-adjusted life years for each participant. Quality-adjusted life years will be the primary outcome measure for the cost-effectiveness analysis and will be used to estimate the incremental cost-effectiveness ratio (ICER) [66]. Pain-related fear: The TSK is a questionnaire assessing beliefs and behaviors related to pain, with a focus on the perception that pain is damaging [77]. The 13-item version will be used. Pain catastrophizing: The PCS is a questionnaire designed to identify catastrophic thoughts about pain [78]. The 13-item version will be used. Pain self-efficacy: The PSEQ measures a patient’s confidence in performing daily activities despite pain [79]. The 10-item version will be used. Symptoms related to central sensitization: The CSI evaluates the frequency of common symptoms associated with central sensitization [80,81]. The 9-item version will be used. Risk of long-term disability: The ÖMPQ-sf is a questionnaire that assesses psychosocial and pain-related factors to predict the risk of long-term disability and delayed return to work in individuals with MSKDs [82]. The 10-item version will be used. Anxiety and depressive symptoms: The HADS is a 14-item questionnaire used to screen the presence of anxiety and depression [70].

#### Secondary Outcomes: Region-Specific Symptoms and Functional Limitations Patient-Reported Outcome Measures

Participants will only complete the region-specific patient-reported outcome measure relevant to their condition. Low back pain: the modified ODI (minimal detectable change=10 points and minimally clinically important difference=10 points) is a 10-item questionnaire assessing the impact of low back pain on activities of daily living [48,83-86]. Neck pain: NDI (minimal detectable change=10 points and minimally clinically important difference=14 points [50,87]) is a 10-item questionnaire measuring self-reported disability related to neck pain [50]. Rotator cuff-related shoulder pain: QuickDASH (minimal detectable change=11 points and minimally clinically important difference=10 points) is an 11-item questionnaire, validated in individuals with rotator cuff–related shoulder pain [88], that assesses difficulty in performing daily activities and the severity of the upper limb symptoms [89]. Anterior knee pain: KOS-ADLS (minimal detectable change=8.3 points and minimally clinically important difference=14 points) is a 14-item knee-specific questionnaire that evaluates symptoms and functional limitations [90].

#### Secondary Outcomes: Participants’ Satisfaction

Participants’ satisfaction with their condition will be assessed at each evaluation time point using the Patient Acceptable Symptom State [64,91]. This measure asks patients whether they consider their current state acceptable and requires them to rate their satisfaction on a 0-100 numeric scale [73]. At the end of the intervention, participants will also evaluate their satisfaction with various aspects of the treatment received. They will rate their overall satisfaction (“not satisfied,” “satisfied,” and “very much satisfied”), the adequacy of treatment duration (“too short,” “long enough,” and “too long”), treatment frequency, and the time spent with the health care providers during sessions (“not enough,” “just right,” and “too much”) using a 3-item Likert scale [73,75,92].

#### Secondary Outcomes: Health Care Resource Use and Health Costs

At the 12-week (covering weeks 0 to 12) and 24-week (covering weeks 13 to 24) follow-up assessments, participants will complete 2 questionnaires: one assessing resource use from the perspective of both public health services and private insurers, and another capturing out-of-pocket costs incurred by participants. For the latter, the Cost for Patients Questionnaire (CoPaQ) will be used, a validated tool that measures patient-related costs, including those incurred by informal caregivers [93,94]. The CoPaQ covers expenses such as copayments, transportation to treatment sessions, childcare, time off work, and lost income. The resource use questionnaire will collect data on health care use, including visits to family physicians, physiotherapists, and other health care providers, as well as medical imaging, laboratory tests, and indirect costs. It will also collect information on each participant’s private health insurance and the extent of coverage for each resource used, where applicable. The average cost of consultations with each type of provider will be determined based on reimbursement rates from both the public and private payers.

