### Intervention

Usual medical care will be provided by family physicians practicing in family medicine groups or university-affiliated family medicine groups, while usual rehabilitation care and stepped care will be provided by physiotherapists practicing in physiotherapy clinics across the Quebec City area. To enhance the generalizability of findings to the broader health care workforce, family physicians and physiotherapists with varying levels of experience, from early-career to experienced clinicians, will be included. Each intervention will have a maximum duration of 12 weeks. All consultation fees with the family physicians and physiotherapists related to the study will be covered by the research team.

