### Stepped Care Group

During the first 6 weeks, participants in the stepped care group will engage in a web-based self-management education program, supplemented by 2 individual educational sessions with a physiotherapist. The first session (60 minutes) will begin with a clinical evaluation by the physiotherapist responsible for the educational intervention, followed by an education session covering the anatomy, function, and diagnosis of the affected area, basics of pain neuroscience, and condition-specific guidance on load management [27]. Participants will also receive strategies for pain and activity (pacing) self-management, optimal sleep and work positions, and key lifestyle factors such as stress management and nutrition [19,63]. The importance of physical activity will be emphasized, with recommendations aligned with World Health Organization guidelines (ie, 150-300 minutes of moderate-intensity activity per week), and adapted to each participant’s condition and physical capacity. Throughout the session, physiotherapists will foster open dialogue, personalizing discussions to address each participant’s needs and goals, answering questions, dispelling myths or misconceptions, providing reassurance, and discussing prognosis. An educational website, developed in collaboration with 7 patient partners, will also be introduced. It offers additional resources, including educational videos, summaries of key topics, and supplementary material for reference. Participants will be encouraged to explore these resources independently during the following weeks. The research team will have access to data on time spent on the website throughout the study.

The second educational session (30 minutes), scheduled 2 to 4 weeks later, will focus on reinforcing key concepts and providing long-term recommendations. The physiotherapist will begin by reviewing the participant’s condition and assessing their understanding of the material from the first session and the website. They will verify whether the participant has engaged with the educational website’s online content, address any remaining questions, offer personalized guidance, and provide recommendations for long-term self-management. While the second educational session will be preferably conducted in person, it may also be held via telehealth, depending on the participant’s preference. Following each session, the physiotherapist will complete a brief REDCap questionnaire documenting the topics discussed.

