If participants become symptom-free before completing the 10 sessions, or if the participant and physiotherapist determine that no further sessions are needed, treatment will be discontinued. Participants will then receive advice, recommendations, and home exercises as appropriate. If needed, they will have the option to resume the intervention within the 12-week period. Participants will not be restrained from using over-the-counter medications for pain relief if deemed helpful. If pain persists, the physiotherapist may refer participants to a family physician for further medical evaluation and management, which may include diagnostic tests (clinical, laboratory, or imaging), pharmacological pain management, and corticosteroid injections. Participants may also be referred to other health care providers (eg, psychologists, occupational therapists, and kinesiologists). However, these referrals will not be managed by the research team, and the associated costs will be the participant's responsibility. After each supervised session, the physiotherapist will complete a short REDCap questionnaire detailing the intervention modalities used, exercises prescribed, any referrals made, and the follow-up plan.

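### Study visits should be counted from the trial's own session forms and priced for each payer, not taken from participant recall over about 12 weeks

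*Protocol article*

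**What the plan says.** All references are to the protocol article.

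- **Source of visit counts.** Under Secondary Outcomes: Health Care Resource Use and Health Costs, "The resource use questionnaire will collect data on health care use, including visits to family physicians, physiotherapists, and other health care providers". The same questionnaire covers imaging, laboratory tests and insurance coverage. The timing is "At the 12-week (covering weeks 0 to 12) and 24-week (covering weeks 13 to 24) follow-up assessments, participants will complete 2 questionnaires"; the second of these captures out-of-pocket costs.
- **Unit prices.** The same section says: "The average cost of consultations with each type of provider will be determined based on reimbursement rates from both the public and private payers".
- **Session records.** For the education sessions (Stepped Care Group): "Following each session, the physiotherapist will complete a brief REDCap questionnaire documenting the topics discussed". For usual rehabilitation: "After each supervised session, the physiotherapist will complete a short REDCap questionnaire detailing the intervention modalities used". For usual medical care: "Following each session, the family physician will complete a brief REDCap questionnaire documenting the management approach used"; this form also lists imaging and laboratory tests ordered.
- **Who pays.** Under Intervention: "All consultation fees with the family physicians and physiotherapists related to the study will be covered by the research team". In both usual care arms, care obtained by referral outside the study is at the participant's expense.
- **Use of the costs.** The Statistical Analysis Plan section computes ICERs for the public health service, the participant and society, with the difference in mean costs as numerator.

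Neither the costing section nor the economic paragraph of the Statistical Analysis Plan section links the session forms or payment records to the cost calculation.

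**The concern.** There are two separate problems.

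**Counting.** The only source named for study visits is memory over about 12 weeks, although a record made at the time of each session is already planned. The arms allow very different numbers of visits, so an error that rises with the number of visits does not cancel between arms. The Introduction names fewer consultations as one of the reasons for expecting lower costs, so the visit difference feeds directly into the secondary objective.

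**Paying.** The trial pays the study fees. A participant who truthfully reports spending and insurance coverage will report about zero for the fee of a study visit, in whichever arm. Physiotherapy that a medical-arm participant obtains by referral is not paid by the trial and will be reported. The same service is therefore free in two arms and charged in the third, and this follows from who pays in the trial, not from the care model. It needs no assumption about memory.

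**Working it through.** The article states no visit count, unit cost or recall error, so there is no figure of its own to reproduce. What follows is an illustration.

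**Inputs from the article (maxima, not expected means)**
- Stepped care: 2 education sessions, plus up to 5 more if unresolved at week 6. With *p* the share unresolved, the maximum mean is 2 + 5*p*.
- Usual rehabilitation: up to 10. Usual medical care: up to 3.

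**Assumptions (no figure in the article)**
- *p* from 0 to 1.
- *u*, the share of visits not reported, 10%, 20% or 30%.

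**Step 1: proportional under-reporting.** Recorded gap = (1 − *u*) × true gap.

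| *p* | Contrast | True gap | *u* = 10% | 20% | 30% |
|---|---|---|---|---|---|
| 0 | Rehabilitation − stepped | 8 | 7.2 | 6.4 | 5.6 |
| 0.5 | Rehabilitation − stepped | 5.5 | 4.95 | 4.4 | 3.85 |
| 1 | Rehabilitation − stepped | 3 | 2.7 | 2.4 | 2.1 |
| 0 | Medical − stepped | 1 | 0.9 | 0.8 | 0.7 |
| 0.5 | Medical − stepped | −1.5 | −1.35 | −1.2 | −1.05 |
| 1 | Medical − stepped | −4 | −3.6 | −3.2 | −2.8 |

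The percentage loss equals *u* whatever the caps, *p* or unit prices, because every visit cost is multiplied by (1 − *u*). Against rehabilitation, this understates the stepped care saving. Against medical care, it understates any extra stepped care visits.

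**Step 2: loss only on visits beyond the third.** Recorded visits = *v* if *v* ≤ 3, otherwise 3 + (1 − *u*)(*v* − 3). At *p* = 0.5 and *u* = 10/20/30%:
- Rehabilitation: 9.3/8.6/7.9. Stepped care: 4.3/4.1/3.9, where for example 0.5 × 2 + 0.5 × 6.6 = 4.3.
- Rehabilitation − stepped: 5.0/4.5/4.0 against 5.5, a loss of 9/18/27%.
- Medical − stepped: −1.3/−1.1/−0.9 against −1.5, a loss of 13/27/40% in visit numbers. These mix physician and physiotherapist visits, so they are not cost percentages.
- At *p* = 0, medical − stepped stays at 1, since neither arm exceeds 3 visits.

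**Step 3: constant error.** If each person omits *e* visits, (10 − *e*) − (2 + 5*p* − *e*) = 8 − 5*p*, which is the true gap. Nothing is distorted.

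**Step 4: the payer problem.** Let *a* be the participant's part of a physiotherapy fee outside the trial, *b* the participant's part of a physician consultation, and *k* the outside physiotherapy sessions per medical-arm participant. Taking participant-reported fees only, at the visit maxima, stepped care minus comparator:

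| Comparator | Fee difference outside the trial | Recorded from self-report |
|---|---|---|
| Usual rehabilitation | *a*(2 + 5*p*) − 10*a* = −*a*(8 − 5*p*) | 0 |
| Usual medical care | *a*(2 + 5*p*) − 3*b* − *ak* | −*ak* |

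Against rehabilitation, the whole fee saving on study visits vanishes. Against medical care, stepped care is credited with avoiding the outside fees *ak*, while its own 2 + 5*p* physiotherapy visits, and the physician fees avoided, count as nothing. No monetary size can be given, because the article states neither *a* nor *b*.

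**The case against.** The strongest reply is that the article does not say the questionnaire is the sole source, or that the forms and payment records will be left out of the costing. It is a condensed account, and the full costing plan may already use them. That is fair as to what will be done. It does not change the fact that the article states a source for visit counts, names no other, and has a better one at hand.

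A second reply is that one instrument used alike in every arm is defensible, and that moving everything to provider forms would make measurement differ by arm. This stands for tests: the physician form records tests ordered, not performed, and tests reached by outside referral from rehabilitation would not appear on any study form. A reader might infer that exact counts of imaging and laboratory tests already exist; they do not. The reply does not hold for study consultations, where a form is stated for three settings. For the second step of stepped care it is only implied, since that step is said to follow the usual rehabilitation approach. Completeness of the provider forms is also not guaranteed, hence the check against fees paid.

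Third, unit prices come from reimbursement rates, insurance coverage is recorded, and the cost questionnaire still captures transport, childcare and lost time. This answers part of the payer point: a total cost can be priced. It does not say how a study visit is divided between participant, insurer and public payer, and the coverage reported for a visit the trial paid for does not show what would apply outside the trial.

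**Conclusion.** The point holds as a modest improvement to the costing method, in two parts.

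**Visit counts.** If under-reporting is proportional to visits, the visit-cost difference between arms is understated by the same fraction, 10% to 30% over the assumed range. This is a risk of unknown size. The documents do not show that recall error grows with the number of visits, and a constant error per person would leave the difference intact.

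**Payer allocation.** Self-reported fees for study visits will be about zero for participants and insurers, while outside referrals are charged to participants. If these amounts are used as reported, the fee component of the participant-perspective ICER is distorted. This rests only on the stated payment arrangements. Travel, lost time and other patient costs are not affected by it.

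Two stronger readings are tempting and not supported. One is that study visits are the main cost driver: the Introduction names consultations and medical investigations together, unranked, and no unit costs are given. The other is that a gap of 8 visits is the expected contrast: it sets the rehabilitation maximum against stepped care with every participant resolved, whereas rehabilitation may stop early and some stepped care participants will probably continue.

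**What to change.** In Secondary Outcomes: Health Care Resource Use and Health Costs, state that:

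1. Study consultations in all arms, including the second step of stepped care, are counted from the per-session REDCap forms and checked against fees paid.
2. In each perspective, a study consultation is valued at the share of the public or private rate which that payer would bear outside the trial.
3. The week-12 and week-24 questionnaires are kept in all arms for care outside the study, for imaging and laboratory tests (with the physician forms as a cross-check only), and for travel, lost time and other patient costs.
4. Study visits are excluded from the questionnaire counts, by instruction to participants or by removal afterwards, so that none is counted twice.

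If the full costing plan already does this, one sentence saying so is enough. No new instrument is needed for counting, provided the session form is also completed in the second step. The cost is a small linkage and de-duplication step, plus a stated assumption on the share each payer would bear.
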